### Setting, location and follow-up

The parturients will be screened for inclusion in the study over an 18-month period at the Department of Obstetrics, Copenhagen University Hospital, Rigshospitalet, a tertiary hospital that performs between 6,000 and 7,000 deliveries per year. Eligible parturients are informed about the study and must provide their written consent within 48 hours after delivery. The duration for each individual participant is approximately 12 weeks and involves five follow-up visits by a midwife at the participant’s home. The timeframes of the follow-up visits are three days (between two and four days), one week (between six and eight days), three weeks (between 19 and 23 days), eight weeks (between seven and nine weeks) and 12 weeks (between 11 and 13 weeks).

### Outcomes and safety measures

The primary outcome is the aggregated change in physical fatigue score within 12 weeks postpartum, as measured by a subscale of the Multidimensional Fatigue Inventory (MFI) [37]. Secondary efficacy outcomes include changes in the Hb concentration, *p-*ferritin, *p-*iron, *p-*transferrin, transferrin saturation, reticulocyte count, mean reticulocyte Hb content, other MFI and Postpartum Questionnaire (PPQ) fatigue items, symptoms of postpartum depression, time of postpartum lactogenesis, time of discontinuation of breastfeeding and transfusion of allogeneic RBCs.

The safety outcomes are discontinuation due to intolerance, frequency, nature and severity of adverse events, vital signs, and *p*-sodium, *p-*potassium, *p-*calcium, *p-*phosphate, *p-*urea, *p-*creatinine, *p-*albumin, *p*-bilirubin, *p*-aspartate aminotransferase and *p*-alanine aminotransferase levels. Other outcomes are maternal milk iron level, anaemia symptoms and gastrointestinal symptoms.

### Questionnaires

We will use the three following self-reported questionnaires: the fatigue measures MFI and PPQ and the depression measure Edinburgh Postnatal Depression Scale (EPDS) [38]. Of these, the MFI includes the scale of physical fatigue, which is the primary endpoint of this investigation.

The MFI has been found to have high feasibility, reliability and validity in chronically anaemic women [39] and in postpartum women [40]. The MFI covers the following dimensions: general fatigue, physical fatigue, reduced activity, reduced motivation and mental fatigue. The MFI consists of 20 statements for which the participant indicates, on a five-point scale, the extent to which the particular statement applies to her. The statements refer to aspects of fatigue experienced during the previous days. Higher scores indicate a higher degree of fatigue.

The PPQ is a novel and yet to be validated instrument that was developed for this study to measure fatigue in parturients [see Additional file 1 (in Danish)]. It consists of a visual analogue scale of how tired the participant is and five questions regarding fatigue. The first question concerns what the participant experiences as most troublesome, pain or fatigue. The second question concerns whether the fatigue is experienced most physically or mentally. For each of the first two questions the participant is asked to underline one of five possible responses. The last three questions explore how the fatigue influences breastfeeding, contact with the newborn and to what extend the participant asks for help with nappy changing. The participant is asked to indicate, on a four-point scale, the extent of the influence of the fatigue. Higher scores from the last three questions indicate a higher degree of fatigue.

The EPDS is a screening instrument that was developed to detect symptoms of depression in puerperal women. A number of studies have confirmed that the EPDS is both reliable and sensitive [41]. The EPDS consists of 10 questions. Participants are asked to underline one of four possible responses that comes closest to how she has been feeling during the previous seven days. The maximum score is 30 and a score of 10 or higher indicates possible depression.

### Monitoring and data collection

The data collection tool for this study is an electronic case report form. Data necessary for analyses and reporting will be entered into a validated and secured data system. Clinical data management is performed in accordance with applicable standards and data cleaning procedures.

A clinical research associate (CRA) from a contract research organisation will monitor the study for protocol compliance, verifying that safety procedures and the rights of participants are being protected. The CRA will also verify that the study is conducted in accordance with the currently approved protocol and any other study agreements, ICH-GCP guidelines and all applicable regulatory requirements. The CRA will also monitor and verify that data are authentic, accurate and complete.

### Number of participants

The following hypothesis will be tested: iron isomaltoside 1000 is superior to standard medical care in the treatment of iron deficiency in women with PPH with or without anaemia, measured primarily by a reduction in physical fatigue. The null hypothesis of no difference between the treatment groups will be tested against the alternative by constructing a two-sided 95% confidence interval of the difference in aggregated change in physical fatigue score from baseline to week 12 between the two treatment groups. The sample size calculations are based on the primary endpoint, aggregated change in physical fatigue score from baseline to week 12. A two-sided significance level of 5% is used and the power is set to 80%.

The use of the physical fatigue subscale of MFI allows a maximum change of 16 points. Based on clinical judgement and consensus between all authors, we wish to see a difference greater than 10% for claiming clinically relevant superiority. Hence, we set the minimal clinically relevant difference to 1.8. In a previous study, the standard deviation was found to be approximately 4.2 [40]. Therefore, 87 patients per treatment group are needed in order to demonstrate superiority. With a margin for missing data and a dropout rate of 13%, 200 women will be included.

### Statistical methods and data analysis

All tests are pre-specified in a statistical analysis plan. The primary analysis population will be the full analysis set, including all randomised participants who received the study drug and have at least one post-baseline physical fatigue score. The primary endpoint is the aggregated change in the physical fatigue score from baseline to week 12. This will be calculated as the area under the curve of the changes in the physical fatigue score from baseline to each visit until week 12, divided by the number of scheduled days (observation period). The area under the curve will be calculated using the linear trapezoidal method and scheduled days. The primary endpoint will be analysed using an analysis of variance model, with treatment and amount of PPH (700 to 1,000 mL or >1,000 mL) as factors, and baseline MFI physical fatigue score as the covariate. The estimated treatment differences (iron isomaltoside 1000 versus standard medical care) expressed as contrasts of the adjusted means will be presented with corresponding 95% confidence intervals and the *P* value. Iron isomaltoside 1000 will be considered superior to standard medical care if the lower limit of the 95% confidence interval is above zero. We will also perform a per protocol analysis excluding participants with major protocol deviations, such as rescue allogeneic RBC transfusion.

All statistical tests of the efficacy endpoints will be two-sided and performed on a 5% significance level. Estimated treatment differences and 95% confidence limits will be presented together with the corresponding *P* value. Continuous secondary endpoints will be analysed by a mixed model for repeated measurements, including visit and treatment-by-visit, and PPH (700 to 1,000 mL or >1,000 mL) as factors, the baseline value as the covariate, and the subject as the random effect. If no baseline value is measured for the endpoint in question, the value at the first measured time will be included as the covariate. An unstructured covariance structure will be used to model the within-subject errors and the estimation method will be a restricted maximum likelihood-based approach. The analysis will be based on the ‘missing at random’ assumption and performed using the data from each observed case. ‘Proportion’ endpoints will be analysed by logistic regression with treatment as the factor. Where relevant, the baseline value of the parameter in question will be included as the covariate. Time to postpartum lactogenesis and time to discontinuation of breastfeeding will be assessed and analysed using Kaplan-Meier curves and compared between treatments using a log-rank test. The laboratory data will be analysed as described for the continuous variables above. Adverse events will be summary tabulated using the latest version of the Medical Dictionary for Regulatory Activities body system and preferred term indicating the number and percentage of participants and the number of events. The number of participants who experience an adverse drug reaction, including suspected unexpected serious adverse reactions, will be compared between treatment groups.

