### Previous studies and current guidelines

International guidelines are available for the treatment of iron deficiency anaemia in pregnancy and the postpartum period [18–21]. These guidelines recommend oral iron supplementation in mild anaemia, intravenous iron in moderate anaemia and when oral iron supplementation is not tolerated, and allogeneic red blood cell (RBC) transfusion in severe and symptomatic cases. These guidelines do not deal with screening for or treatment of iron deficiency without anaemia.

Denmark has no published national guideline on the screening or treatment of postpartum iron deficiency with or without anaemia. In clinical practice, doctors usually recommend oral iron supplementation to parturients with PPH, and RBC transfusion to those with severe symptoms of anaemia. Since puerperal women with a Hb level of ≤6.5 g/dL (4.0 mmol/L) often have severe symptoms of anaemia, we will not include these parturients in the study.

No prospective randomised clinical studies have yet assessed the effect of intravenous iron supplementation in comparison to standard medical care in women after PPH with a clinical outcome as the primary endpoint. There have been 10 randomised controlled studies that have compared intravenous iron to oral iron supplementation in women with diagnosed postpartum iron deficiency anaemia [22–31]. The inclusion criteria of these studies were Hb concentration up to 10 days after delivery, and the primary study endpoints were Hb concentration, iron parameters and comparisons thereof. Generally, these studies have demonstrated improvement of Hb and iron parameters, favouring intravenous iron. With regard to safety, oral iron was associated with gastrointestinal side effects in up to 30% of the participants, with a compliance rate as low as 50%. These findings must be balanced against the very low risk of severe hypersensitivity reactions with intravenous iron [12].

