### Intervention

The participants will be randomised to either standard medical care or iron isomaltoside 1000. Standard medical care (current treatment practice) at the Department of Obstetrics, Copenhagen University Hospital, Rigshospitalet is typically to recommend women with PPH to either continue oral iron supplementation, as during pregnancy (the Danish Health and Medicines Authority recommends 40 to 50 mg oral iron supplementation daily [35]), or to take 100 mg oral iron one or two times daily for a variable time period. The actual use of iron supplementation, including specific preparation, dose and duration of treatment, will be monitored at each follow-up visit.

Immediately after acute bleeding such as PPH, the Hb level is inaccurate for calculating individual dosing of iron supplementation. Hence, the iron isomaltoside 1000 fixed dosage in this study is based on the expected iron deficiency in women after PPH. Body iron stores are approximately 500 to 750 mg and the average iron loss through PPH is approximately 500 mg, as 500 mL blood loss equals 250 mg iron loss [4]. In previous studies of women with postpartum anaemia, oral iron treatment dosages were 130 to 200 mg per day over a period of 42 to 84 days, resulting in a total average dose of 11.088 mg [23–27]. The intestinal iron absorption varies considerably but is believed to be a maximum of 10% [36], resulting in a total expected absorption of 1,100 to 1,200 mg. Thus, the cumulated iron dosages in these studies are in accordance with the chosen treatment dose in this study.

In the group allocated to iron isomaltoside 1000, Pharmacosmos A/S, Holbaek, Denmark, the iron replacement dose is set to 1,200 mg. The dose is diluted in 100 mL 0.9% sodium chloride, Fresenius Kabi AG, Bad Homburg, Germany, and administered over a period of approximately 15 minutes. No test dose is applied. Participants with a pre-pregnancy weight <45 kg will receive a reduced single dose of 1,000 mg iron isomaltoside 1000, administered in the same fashion. In both treatment groups, participants may be given a ‘rescue’ allogeneic RBC transfusion if this procedure is clinically indicated.

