## Discussion

The aim of this study is to compare a new treatment option (iron isomaltoside 1000) to standard medical care. The choice of the latter active comparator, ‘the drug of first choice’, enables us to use the results of this study for assessing the potential additional benefit of iron isomaltoside 1000 in a clinical setting.

The standard medical care treatment group does not receive a general specified recommendation of oral iron supplementation. We considered that standard treatment, as defined by the individualised regimen chosen by the parturient and her midwife, was the proper comparator. A pregnant woman usually takes oral iron supplementation from early pregnancy and finds a preparation and a dose that is suitable for her. A general fixed regimen might cause gastrointestinal side effects in some individuals, and a possible insufficient effect in others. Therefore, the fixed regimen would be suboptimal as a comparator compared with the standard individualised regimen, which is current practice in the Capital Region of Denmark. The actual use of oral iron, including specific preparation, dose and duration of treatment, is registered at each follow-up visit.

The individualised regimen design implies that we were not able to blind the randomisation in this trial. Also, since iron tablets colour the stools, we assessed that a double-blinded design would be unfeasible and would not contribute additional scientific merit. Accordingly, most previously published randomised controlled trials with iron treatment of women after childbirth have not been double-blinded [23–27].

The strength of this trial is the fact that it will be conducted at a single centre. This means that the standard medical care is less diverse than it might otherwise be and we can ensure a full overview of all parturients with PPH ≥700 mL in the time period of inclusion, which will enable us to collect detailed information about those excluded and the reasons why not.

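### The primary analysis set requires receipt of a study drug that only the iron arm is assigned, so the condition can exclude only un-infused iron-arm women, after open randomisation

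*Protocol article*

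**What the plan says.** Under Statistical methods and data analysis, the primary analysis population is the full analysis set, "including all randomised participants who received the study drug and have at least one post-baseline physical fatigue score".

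The Intervention section sets out the arms: "The participants will be randomised to either standard medical care or iron isomaltoside 1000". A named product at a fixed amount is given in the iron arm only. For standard care, the section describes what the department usually recommends and then says: "The actual use of iron supplementation, including specific preparation, dose and duration of treatment, will be monitored at each follow-up visit". The Discussion confirms that this was deliberate: "The standard medical care treatment group does not receive a general specified recommendation of oral iron supplementation".

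Study design states that the trial is open-label. Later in the Discussion, a subjective endpoint in an open-label study is acknowledged as an inherent weakness.

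On transfusion, the Intervention section allows both arms a rescue "allogeneic RBC transfusion if this procedure is clinically indicated". Outcomes and safety measures ends its list of secondary efficacy outcomes with "time of discontinuation of breastfeeding and transfusion of allogeneic RBCs". Statistical methods adds a per-protocol analysis "excluding participants with major protocol deviations, such as rescue allogeneic RBC transfusion".

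**The concern.** A condition of receipt is harmless when non-receipt cannot depend on the allocated arm, as in a blinded trial where both arms are dosed alike. Here the arms are not alike. One is assigned an infusion that a woman either does or does not receive. The other is assigned usual care, which has no dosing event that could be missed. The same sentence therefore acts as a filter in the iron arm and does nothing in the control arm.

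The filter also acts after randomisation, when the woman and the staff know the allocation. If the women who go un-infused differ in fatigue from those who are infused, for example because they are more unwell or less motivated, removing them shifts the iron-arm mean. Their counterparts in the control arm stay in. At stake is whether the set that decides superiority is the set that was randomised.

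**Working it through.** **1. Which arm can the condition act on?**

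| Arm | What is assigned | Can receipt fail? |
|---|---|---|
| Iron isomaltoside | One infusion of a named product | Yes, if the infusion is not given |
| Standard medical care | Individualised recommendation; oral iron use recorded at visits | No receipt event is defined |

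The workable reading is that receipt is checked in the iron arm only. The other condition in the sentence, at least one post-baseline fatigue score, also selects after randomisation, but it applies to both arms.

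**2. The plan's own figure.** Inputs from Number of participants: difference 1.8, standard deviation 4.2, two-sided 5%, power 80%. The normal approximation gives 86 per group. The two-sample t calculation gives 86.4, rounded up to 87, as stated. Allowing 13% dropout, 174 / 0.87 = 200, as stated. The sample size is sound and this point does not affect it.

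**3. Size of the shift.** Let k of n iron-arm women be excluded as un-infused. Let D be the difference in mean aggregated change between the included and the excluded women of that arm. Then

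mean(included) − mean(all) = (k/n) × D,

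and the treatment difference moves by the same amount because the control arm is untouched. From the document, n = 200/2 = 100. The document gives neither k nor D; the values below are assumptions.

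| k | D = 2 points | D = 4 points |
|---|---|---|
| 1 | 0.01 × 2 = 0.02 (0.02/1.8 = 1%) | 0.01 × 4 = 0.04 (0.04/1.8 = 2%) |
| 5 | 0.05 × 2 = 0.10 (0.10/1.8 = 6%) | 0.05 × 4 = 0.20 (0.20/1.8 = 11%) |

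A D of 4 is severe: 4/4.2 = 0.95 standard deviations.

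**4. Effect on the test.** Standard error = 4.2 × √(2/100) = 0.594, held at 100 per arm. If the true difference among all randomised women is zero and the estimate is shifted by b, the two-sided rejection rate is 1 − Φ(1.96 − b/0.594) + Φ(−1.96 − b/0.594).

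- b = 0.04: 0.0505
- b = 0.10: 0.0533
- b = 0.20: 0.063

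**5. Effect on power.** With 100 per arm and a 1.8-point difference, power is 85.4%. With 5 iron-arm women excluded it is 84.5%. Loss of power is not the issue.

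**6. Transfusion passages side by side.** Intervention permits it, Outcomes counts it as efficacy, and Statistical methods names it as a major protocol deviation. If treatment affects the need for transfusion, the per-protocol set is selected on something the treatment may change.

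**The case against.** The strongest reply is that the sentence is shorthand in a journal article and probably means study treatment, with the detail left to a statistical analysis plan that is not shown. The opportunity for non-receipt also looks small: consent is given within 48 hours of delivery, the infusion takes about 15 minutes, and the Background wants the deficit corrected before the woman leaves hospital. No direction of bias can be shown. All of this limits the size of the problem. It does not remove it, because the article itself fixes the rule, and under the workable reading the rule still acts on one arm only.

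It can also be said that the per-protocol analysis is additional and departs from the randomised comparison by design, as any such analysis does. A transfusion can be clinically allowed, counted as an outcome and still be a reason to leave a per-protocol set. Nothing in the text removes transfused women, or their later scores, from the full analysis set. This stands. What is left is a loose label and a caution about interpretation.

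Finally, replacing the receipt condition still leaves a set that requires a post-baseline score. That is true, but the requirement is the same in both arms.

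**Conclusion.** The point holds as a one-sided, post-randomisation exclusion in the definition of the primary set. It is a risk to the comparison, not a demonstrated break. With 100 per arm, a standard deviation of 4.2, 1 to 5 un-infused women excluded and a 4-point difference, the shift is 0.04 to 0.20 points, or 2% to 11% of the 1.8-point target, and the type I error is about 0.0505 to 0.063. The number excluded and the 4-point difference are assumptions, and the true count may well be at the low end.

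Three stronger inferences are not supported:

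- **No control woman qualifies.** This follows from the literal wording but is plainly not intended in a two-arm comparison.
- **Control women who took no tablets would be dropped.** Someone assuming 20% of controls and a 2-point difference would get 0.20 × 2 = 0.40 points, or 22% of the target. But no passage makes oral iron a study drug, and a woman who takes none has still had standard care. The Background figure for oral iron, "with a compliance rate as low as 50" per cent, describes compliance in earlier trials, not the share who took nothing.
- **The per-protocol set undermines the superiority claim.** The claim rests on the full analysis set. The transfusion passages call for reconciliation only, and no view is taken here on the clinical rule.

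**What to change.** Define the primary set as all randomised women with at least one post-baseline physical fatigue score, analysed in the arm to which they were randomised regardless of treatment received. If the statistical analysis plan already says this, bring the article's description into line with it.

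The cost is a change of wording, provided that un-infused women are still followed and their scores collected. The downside is slight dilution of the estimated effect if a few iron-arm women go undosed.

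Secondarily, reconcile the three statements on rescue transfusion, and state that the per-protocol result is supplementary and is not to be read as confirming the primary one.

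### The superiority rule points the wrong way: as written, it is met only when iron isomaltoside leaves women significantly more fatigued than standard care

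*Protocol article*

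**What the plan says.** Five statements in the protocol article bear on the direction of the primary comparison.

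- **Scale** (Questionnaires, on the Multidimensional Fatigue Inventory): "Higher scores indicate a higher degree of fatigue".
- **Direction of benefit** (Number of participants): superiority is "measured primarily by a reduction in physical fatigue".
- **Endpoint** (Statistical methods and data analysis): an "area under the curve of the changes in the physical fatigue score from baseline to each visit until week 12", which is then averaged over the planned length of follow-up.
- **Contrast** (same section): "The estimated treatment differences (iron isomaltoside 1000 versus standard medical care) expressed as contrasts of the adjusted means".
- **Decision rule** (same section): "Iron isomaltoside 1000 will be considered superior to standard medical care if the lower limit of the 95% confidence interval is above zero".

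The sample-size section gives the target difference without a sign ("Hence, we set the minimal clinically relevant difference to 1.8") and takes the SD from an earlier study ("the standard deviation was found to be approximately 4.2").

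**The concern.** The first four statements make a benefit of iron a negative number, while the rule asks for a positive one. If fatigue falls more under iron, its mean change is more negative, the difference iron minus standard care is below zero, and a convincing result puts the whole interval below zero. The rule instead requires the whole interval to lie above zero. That happens only when the iron group's fatigue falls significantly less than the standard-care group's, or rises more.

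This is the only confidence-interval criterion the article gives for the primary objective. Applied literally, it would almost never recognise the benefit the trial was designed to find, and it would report a significant disadvantage as superiority.

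**Working it through.** **Inputs.** From Number of participants: difference 1.8, SD 4.2, two-sided alpha 5%, power 80%, 87 per group, 13% dropout, 200 in total. From Study design: 1:1 allocation. Conventions assumed, because the article does not spell them out: change = visit minus baseline; difference d = iron minus standard care.

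**1. Reproduce the plan's sample size.**
- Normal approximation: n = 2 × (1.960 + 0.842)² × 4.2² / 1.8² ≈ 85.5, so 86 per group.
- With the t distribution: 87 per group, power 0.803. This is the stated figure.
- Dropout: 2 × 87 / (1 − 0.13) = 174 / 0.87 = 200.

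The calculation depends only on the size of 1.8, not its sign, so it is sound and says nothing about direction.

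**2. Sign of a benefit under the endpoint definition.** Take invented mean changes at days 0, 3, 7, 21, 56 and 84, with iron better at every visit:
- Iron: 0, −2, −4, −6, −7, −8. Trapezoidal area = −3 − 12 − 70 − 227.5 − 210 = −522.5; divided by 84, −6.22.
- Standard care: 0, −1, −2, −4, −5, −6. Area = −1.5 − 6 − 42 − 157.5 − 154 = −361; divided by 84, −4.30.
- d = −6.22 − (−4.30) = −1.92.

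Iron is better throughout and d is negative.

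**3. Standard error and critical difference.**
- SE = 4.2 × √(2/87) = 0.637.
- The lower 95% limit exceeds zero when the estimate exceeds 1.96 × 0.637 = 1.248 (normal), or 1.257 with t on 172 degrees of freedom.

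**4. An observed benefit equal to the planned effect.** If the estimate is −1.8, the interval is −1.8 ± 1.96 × 0.637, about −3.05 to −0.55. This is a clear benefit, yet the lower limit is far below zero and the written rule is not met.

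**5. Probability of declaring superiority** (normal approximation):

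| True d (iron minus standard care) | Rule as written: lower limit > 0 | Reversed rule: upper limit < 0 |
|---|---|---|
| −1.8 (iron better) | 8.5 × 10⁻⁷ | 0.807 |
| 0 | 0.025 | 0.025 |
| +1.8 (iron worse) | 0.807 | 8.5 × 10⁻⁷ |

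With the t critical value the small probability is about 8 × 10⁻⁷. Only the reversed rule delivers the planned 80% power. The chance of a false claim when there is no difference is the same under both.

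**The case against.** The strongest reply is that the sign is inferred. The article never writes the change as visit minus baseline, and it says versus rather than minus. It also speaks of effects as positive amounts: a reduction in fatigue, an improvement in the score, an unsigned 1.8, a maximum change of 16 points. If change meant reduction (baseline minus visit), or if the contrast were standard care minus iron, the rule would be correct. That much is true, but the article states neither. Changes running from baseline to each visit, and iron named first in the contrast, both point to the ordinary reading, and an unsigned effect size is normal in any sample-size section.

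A second reply is that the statistical analysis plan, which is not available here, may have the direction right, and that a sensible analyst would see the intent. The estimate, interval and P value would be the same apart from sign. This limits what can be said about what the trial would actually report. It does not repair a rule that the article states in full, and a correct analysis plan would then disagree with the published protocol on the primary criterion. In an open-label, company-sponsored trial with a self-reported endpoint, the direction should be settled on the record and not by interpretation once results are known.

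Two limits on the claim do stand. Worse means worse relative to standard care: both groups may improve, and the rule is met if iron improves significantly less. And the probabilities above are the planned power calculation with the sign turned round. They show the consequence of literal use and are not separate evidence of the error.

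**Conclusion.** The concern holds. Under the article's own scale, endpoint and contrast, the superiority rule is reversed: at the planned effect it is met with probability about 8 × 10⁻⁷ instead of 80%, and it is met about 80% of the time if iron is worse by the same amount. This rests on the usual sign conventions, which the text supports and nowhere overrides, and on literal application of the rule. Sample size, significance level and power are unaffected. Because the sentence sets the decision for the primary objective, it must be corrected.

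**What to change.** Replace the rule with: iron isomaltoside 1000 is declared superior if the upper limit of the two-sided 95% confidence interval for the adjusted mean difference in aggregated change (iron isomaltoside minus standard medical care, change = visit minus baseline) is below zero.

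An equally valid route keeps the present rule and states explicitly either that the endpoint is a reduction (baseline minus visit) or that the contrast is standard care minus iron. Only one of these should be adopted, since reversing two signs would restore the error.

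Check that the statistical analysis plan and its table shells use the same convention, and make the correction on record before results are known. The cost is one sentence in the protocol, plus a matching edit in the analysis plan if it carries the same wording. No change to data collection, sample size or conduct is needed.

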**Figure 1 Fig1:**
[figure not shown]
**Trial flow.** Women with postpartum haemorrhage ≥700 and ≤1,000 mL or PPH >1,000 mL and haemoglobin >6.5 g/dL (4.0 mmol/L) within 48 hours of delivery will be screened for inclusion and exclusion and asked for consent to participate. Baseline questionnaires are completed and blood samples are taken. The participants are randomised to either intravenous iron isomaltoside 1000 or standard medical care. Follow-up visits with completion of questionnaires, blood samples and maternal milk samples are performed at three days, and one, three, eight and 12 weeks after intervention. (EPDS: Edinburgh Postnatal Depression Scale; Hb: haemoglobin; HELLP: haemolysis, elevated liver enzymes, and low platelet count; MFI: Multidimensional Fatigue Inventory; PPH: postpartum haemorrhage; PPQ: Postpartum Questionnaire; RBC: red blood cells; subMFI: subscale of the Multidimensional Fatigue Inventory; subPPQ: subscale of the Postpartum Questionnaire).

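### Where an endpoint has no baseline, the first measured value becomes the covariate; for maternal milk iron that value is post-treatment and would bias the comparison

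*Protocol article*

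**What the plan says.** The rule is in the protocol article under Statistical methods and data analysis. The model is introduced with "Continuous secondary endpoints will be analysed by a mixed model for repeated measurements, including visit and treatment-by-visit"; the bleeding stratum is a further factor and the baseline value is the covariate. The fallback follows: "If no baseline value is measured for the endpoint in question, the value at the first measured time will be included as the covariate". Later in the same section: "The laboratory data will be analysed as described for the continuous variables above".

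The legend of Figure 1 shows what is available before randomisation: "Baseline questionnaires are completed and blood samples are taken". Milk is not mentioned there. It appears only at follow-up: "maternal milk samples are performed at three days, and one, three, eight and 12 weeks after intervention".

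Outcomes and safety measures puts milk iron in its last group, after the secondary efficacy and safety outcomes: "Other outcomes are maternal milk iron level, anaemia symptoms and gastrointestinal symptoms".

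The primary analysis does not use the fallback. Its covariate is the "baseline MFI physical fatigue score as the covariate".

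**The concern.** A baseline covariate is safe in a randomised comparison because treatment cannot have influenced it. A value first measured at a follow-up visit lacks that property, since by then the intravenous arm has had its infusion. If treatment has already moved the endpoint, conditioning on the moved value takes part of the effect out of every later contrast.

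There is a second consequence, which is an inference. A value that enters as the covariate would normally no longer be modelled as a response, so the difference at the visit closest to the infusion would not be estimated. The article does not say this outright.

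At stake is the between-arm comparison for milk iron. The main conclusion of the trial is not.

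**Working it through.** **Which endpoints can trigger the rule**

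- Primary endpoint: uses the true baseline score, so no.
- Blood endpoints (Hb, iron parameters, reticulocyte measures, blood chemistry): blood is taken at baseline, so no on the text shown.
- Fatigue and depression questionnaires: completed at inclusion (Abstract and Figure 1), so no.
- Lactogenesis and end of breastfeeding: Kaplan-Meier curves and log-rank test, so not in this model.
- Maternal milk iron: no baseline sample listed, first sample at three days. It falls under the rule if it counts as laboratory data; no other method is given for it.
- Anaemia and gastrointestinal symptoms: the article does not show whether they have a baseline or are continuous.

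**What the model then estimates**

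The plan gives no figure for this rule, so there is none to reproduce. Let delta_t be the true treatment effect at visit t, delta_1 the effect at the first measured visit, and rho the within-woman correlation between the two visits. The within-arm slope of the later value on the first is

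b = rho × SD_t / SD_1,

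and the adjusted contrast is

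delta_t − b × delta_1, instead of delta_t.

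**Inputs**

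The effects and correlations below are assumptions. They take equal variances and one common correlation, so that b = rho. The plan specifies an unstructured covariance, under which b could differ.

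*Sustained effect of 0.5 SD at every visit:*

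| rho | Calculation | Reported effect | Loss |
|---|---|---|---|
| 0.3 | 0.5 − 0.3 × 0.5 | 0.35 SD | 30% |
| 0.5 | 0.5 − 0.5 × 0.5 | 0.25 SD | 50% |
| 0.7 | 0.5 − 0.7 × 0.5 | 0.15 SD | 70% |

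*Fading effect of 1, 0.8, 0.5, 0.2, 0 SD over the five visits, rho = 0.5:*

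| Visit | True | Calculation | Reported | Reading |
|---|---|---|---|---|
| 2 | 0.8 | 0.8 − 0.5 | +0.3 | shrunk |
| 3 | 0.5 | 0.5 − 0.5 | 0 | shrunk to zero |
| 4 | 0.2 | 0.2 − 0.5 | −0.3 | sign reversed |
| 5 | 0 | 0 − 0.5 | −0.5 | false effect where the truth is zero |

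*Effect of 0.5 SD at the first visit only, zero afterwards:* later visits are reported at −0.15, −0.25 and −0.35 SD for rho 0.3, 0.5 and 0.7.

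*No first-visit effect (delta_1 = 0):* the subtracted term is zero and so is the bias.

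**Simulation check**

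The check used 100 women per arm, 2,000 runs and a per-visit analysis of covariance on the first value, as a stand-in for the treatment-by-visit contrasts. The mean estimates agreed with the formula.

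- Sustained 0.5 SD effect: power per visit was about 69%, 50% and 28% at the three correlations, against about 94% without the covariate.
- First-visit-only effect: a significant result in the wrong direction appeared at each later visit in about 19%, 50% and 91% of trials, against a nominal 2.5% in that direction.

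**The case against.** The strongest reply is about reach. The fallback follows the sentence on continuous secondary endpoints, and milk iron is not listed as one. It comes under the rule only through the sentence on laboratory data. That is an inference, though a natural one. A reader might infer that laboratory or secondary endpoints as a class are compromised. The article does not support this: blood is sampled at baseline, and no second exposed endpoint can be named.

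The size is also open. Nothing in the article says how large an early effect on milk iron might be, or that one is expected. A reader might suppose that an early peak in milk iron is what the trial hopes to detect. The article lists the outcome without any such hypothesis. If treatment has not moved milk iron by three days, the rule does little harm.

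Finally, the covariate buys precision, and at high correlation the gain is not small. That stands as a cost of the fix. It does not justify the rule, because the precision then attaches to a contrast other than the randomised effect.

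An unseen analysis plan does not remove the point, since the article itself states the rule.

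**Conclusion.** The rule is wrong as written. Where it applies, the model estimates delta_t − b × delta_1 and not the treatment effect. On the text shown it reaches maternal milk iron only, on the reading that this is laboratory data.

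The bias scales with the first-visit effect. It ranges from about zero when there is none to a loss of 30% to 70% of a sustained effect at correlations of 0.3 to 0.7. Reversal is possible but not general: it needs a later effect smaller than b × delta_1. In the fading example a true effect changes sign at visit 4 only, so it would be too strong to say that all later signs are wrong. All these sizes rest on assumed effects, equal variances and a common correlation.

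A reader might also infer that the fatigue result is at risk. It is not, because the primary analysis adjusts for a true baseline. Severity is minor to moderate.

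**What to change.** Delete the fallback sentence and replace it with wording such as: *Only values obtained before randomisation are used as covariates. Where none exists, the model contains visit, treatment-by-visit and PPH stratum only, and the first measured value is kept as a response.* It would help to state in the same place that maternal milk iron is analysed by this model.

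Under the plan's missing-at-random assumption, each visit contrast then estimates delta_t, and the three-day difference is estimated as well. No new data are needed, and neither the sample size nor the primary analysis changes.

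The cost is wider intervals at later visits. Under the same assumptions with a first-visit effect of 0.5 SD, the widening factor is 1 / sqrt((1 − rho²) × (1 + 0.5²/4)):

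- rho 0.3: 1 / sqrt(0.91 × 1.0625) = 1.02, about 2%
- rho 0.5: 1 / sqrt(0.75 × 1.0625) = 1.12, about 12%
- rho 0.7: 1 / sqrt(0.51 × 1.0625) = 1.36, about 36%
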